### Interim analyses {21b}

An interim data analysis will be conducted once all immediate post-test data (Timepoint 2) have been collected. Final analyses will be performed after the completion of data collection at follow-up (Timepoint 3). This interim analysis will ensure data quality and participant safety before the follow-up phase. The intervention will be stopped if a significant increase in clinically concerning eating disorder symptoms or other adverse effects is detected.

Interim results will be shared internally with the research team, advisors, and relevant stakeholders, and may also be presented at academic conferences. These findings will not be published until the follow-up phase is complete; however, we may conduct and share secondary analyses of baseline variables prior to final publication.

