**Methods:**

We will recruit 1250 adolescents in 7th–10th grade (aged 11–17 years) to participate in a two-arm, cluster-randomized, open-label, controlled superiority trial in Colombia. Participating schools will be recruited by the research team. Participants will be randomized at the school level (1:1). Randomization blocks stratified by socioeconomic status (high vs. low) and geographical area (rural vs. urban) will be used to assign schools to either: (a) a school-based, four-session group intervention delivered over 2–4 weeks by trained facilitators (*n* = 625) or (b) a waitlist control group that will receive the intervention only after follow-up (*n* = 625). Participants need to be aged 11–17 years old, attending a participating school and class in grades 7 to 10, have written parental consent, and give written assent to be eligible for participation in this study. Individuals who cannot understand spoken or written language, or who do not have parental consent to participate, will be excluded. Primary outcomes are media literacy and body dissatisfaction. Secondary outcomes include appearance comparison, thin ideal internalization, curvy ideal internalization (girls only), drive for muscularity (boys only), eating disorder symptoms, and general wellbeing. Additional exploratory outcomes include risky appearance-altering behaviours (girls only), colourism, and skin colour satisfaction. Furthermore, adverse outcomes will be recorded.

Outcome assessments will happen pre-intervention (baseline; Timepoint 1), 1-week post-intervention (immediate post-test; Timepoint 2), and 9–12 months post-intervention (follow-up; Timepoint 3).

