**Discussion:**

Based on pilot data, we hypothesise that the intervention group will demonstrate increased media literacy and decreased body dissatisfaction at post-test and follow-up. We also anticipate improvements in secondary outcomes. This will be the first cluster RCT to evaluate the effect of a culturally adapted body image intervention in Colombia. This trial has been registered in the ISRCTN Registry (ISRCTN15802562, https://doi.org/10.1186/ISRCTN15802562). First enrolment was on 26th of August 2025.

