### Trial design {8}

In this two-arm cluster-randomized, open-label, controlled superiority trial, we will compare changes in primary and secondary outcomes in participating adolescents randomized to receive either the intervention or a wait-list control condition in a parallel group design over the first 9–12 months of the study. The group allocation ratio is 1:1, clustered by school and stratified by geographical location (urban/rural), socioeconomic position (high/low), and funding status (state/private). Participants in the waitlist control group will receive the intervention after follow-up data collection is concluded.

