### Intervention description {11a}

The intervention, called “Soy Como Soy”, is a four-session, school-based intervention designed to promote positive body image (thus decreasing body dissatisfaction) and increase media literacy among adolescents in Colombia. Every session lasts 45 mins and is intended for mixed-gender classroom groups of children aged 11–17 years in their respective class age groups (20–40 participants).

The program targets the reduction of appearance-related pressures by teaching participants to critically analyse media messages, resist unrealistic appearance ideals, and support themselves and others in valuing non-appearance-related qualities. Each session incorporates psychoeducation, interactive discussions, and self-reflection exercises. The program is aligned with evidence-based change techniques for body image interventions [14] and has been pilot-tested in both Nicaragua [11] and Colombia (manuscript in preparation).

All sessions will be administered within a timeframe of 2 to 4 weeks, with either one or two sessions per week, depending on the school’s preference and availability. All sessions will be delivered during usual school hours and in a classroom setting. The facilitators will provide all materials necessary for the sessions (e.g. comic-based storyboards, paper, whiteboard markers).

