## Trial status

Recruitment has started on the 13th of August 2025. The current protocol is version 2 of the 4th of December 2025. Recruitment is estimated to be completed by August 2027.

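### The interim safety look waits for all post-test data, so on the stated dates it comes about 11–16 months after the first follow-ups fall due, and its stop rule can reach only waitlist delivery

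*Protocol article*

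**What the plan says.** Interim analyses {21b} fixes three things about a single look at the data.

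- Trigger: "An interim data analysis will be conducted once all immediate post-test data (Timepoint 2) have been collected".
- Purpose: "This interim analysis will ensure data quality and participant safety before the follow-up phase".
- Action: "The intervention will be stopped if a significant increase in clinically concerning eating disorder symptoms or other adverse effects is detected".

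The dates that bear on this stand elsewhere in the article. The abstract's Discussion says "First enrolment was on 26th of August 2025", and Trial status says "Recruitment is estimated to be completed by August 2027". Intervention description {11a} says "All sessions will be administered within a timeframe of 2 to 4 weeks". The abstract's Methods put the post-test (T2) one week after the intervention and the follow-up (T3) 9–12 months after it. For the control arm, Trial design {8} says "Participants in the waitlist control group will receive the intervention after follow-up data collection is concluded". The comparator section {6b} likewise places waitlist delivery after follow-up assessments.

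**The concern.** The trigger, the purpose and the action do not fit together. A look that needs T2 from every school cannot come before follow-up starts if the early schools reach T3 while later schools are still enrolling. A rule to stop the intervention also has little left to stop once every intervention school has completed its T2.

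This matters because {21b} describes the only interim comparison of questionnaire scores between arms. Scores on the eating disorder questionnaire (EDE-QS) could exist from late September 2025. As written, they are not compared between arms for safety until recruitment has closed, and new intervention schools keep starting in the meantime. The participants are aged 11–17, and Eligibility criteria {10} does not exclude those with active eating disorders. If waitlist schools are served after their own follow-up, some could receive the programme before the look that is meant to decide whether they should.

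**Working it through.** The article gives no interim date, so the check is calendar arithmetic on its stated dates. Two assumptions are needed: sessions start at enrolment, and the last school enrols at some point in August 2027.

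**First schools**
- Sessions end: 26 August 2025 + 2 or 4 weeks = 9 or 23 September 2025.
- T2: + 1 week = 16 or 30 September 2025.
- T3 due: end of sessions + 9 to 12 months = 9 June to 23 September 2026.

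**Last school**
- T2: 1 to 31 August 2027 + 3 to 5 weeks = 22 August to 5 October 2027. This is the earliest the interim can be triggered.

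**Gap between the first T3 and the interim**
- Smallest: 23 September 2026 to 22 August 2027 = 333 days (10.9 months).
- Largest: 9 June 2026 to 5 October 2027 = 483 days (15.9 months).
- Counting from the recruitment start in Trial status (13 August 2025) instead gives 11.4 to 16.3 months.

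**When the conflict would disappear**
- Latest last enrolment = first T3 minus the 3 or 5 weeks to T2.
- 9 June 2026 − 3 weeks = 19 May 2026; 23 September 2026 − 5 weeks = 19 August 2026.
- That is roughly 12–15 months earlier than the estimated end of recruitment.

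**What the stop rule can reach**
- An intervention school's T2 comes one week after its last session. All T2 data collected therefore implies all intervention-arm sessions delivered. This needs no dates.
- What remains is waitlist delivery. If it waits until follow-up has ended across the trial, the interim precedes all of it and the rule can act on up to 625 pupils.
- If it follows each school's own T3, the early waitlist schools become due before the interim. Assuming steady enrolment over a span of 705–735 days, the share of schools with T3 due before the interim is (span + 7 − F)/span, where F is 9 or 12 × 30.44 days. This gives 49–64%. With one third of enrolment in the first half of the span it is 33–52%, and with two thirds 66–76%. The share matters only for waitlist schools and only on this reading.

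**Precision of an earlier look at half the schools**
- Sample size {14} gives ICC 0.046 and m = 25, assumed here to hold for EDE-QS. Design effect = 1 + 24 × 0.046 = 2.104.
- Half the schools: 281–312 per arm (with and without 10% attrition), so effective n = 134–148 per arm.
- 95% half-width = 1.96 × √(2/n) = 0.24 to 0.23 SD.
- All schools: 562–625 per arm, effective n = 267–297, half-width 0.17 to 0.16 SD.

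**The case against.** The strongest reply is that safety does not depend on this look. Under {11b}, facilitators watch for distress, remove pupils and report at once, and multiple adverse events end the study. Under {22}, events go promptly to the ethics committee and to the advisory group, which {5d} describes as independent and meeting twice a year. Under {6b}, waitlist delivery is reconsidered if severe outcomes emerge. The pilot saw no adverse events, and the intervention is four 45-minute classroom sessions. All of this stands and lowers the severity. It does not remove the inconsistency, because these routes depend on observed or reported events and none compares EDE-QS scores between arms.

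It is also fair that August 2027 is an estimate and that recruitment ends when the sample is reached. The dates above are therefore indicative, although enrolment would have to finish about a year early for the text to hold. A natural reading of {8} is that waitlist delivery follows trial-wide follow-up, and on that reading the rule keeps real force.

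Two stronger readings are not supported. A reader might infer that every pupil who reaches T3 before the interim is put at risk. T3 is a questionnaire and adds no exposure, so for intervention-arm pupils it changes nothing. A reader might also infer that an early look would spare all intervention pupils not yet started. That assumes harm is detected with certainty and acted on at once. With a half-width of 0.23–0.24 SD, a true mean difference of that size would be detected only about half the time, and paper questionnaires must first be entered by hand.

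**Conclusion.** The concern holds in a limited form, and the text should be changed. On the stated dates the interim falls about 11–16 months after the first schools' follow-up is due, so it cannot act ahead of the follow-up phase. This rests on recruitment running close to its estimated end and on sessions starting at enrolment. It fails only if the last school enrols by about May–August 2026. Independently of any date, the stop rule cannot affect intervention-arm sessions. It can act only on waitlist delivery, and only in full if that delivery waits for trial-wide follow-up, which {8} and {6b} do not settle. The documents do not show that pupils are unprotected: event-based monitoring runs throughout. What is missing is a comparison of scores between arms early enough to inform a decision.

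**What to change.** In {21b}:

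1. Add a safety-only comparison between arms of EDE-QS and adverse events when T2 is complete for a fixed early batch of schools, for example the first half. Send it to the existing advisory group, examine no efficacy outcomes, and require no pause in enrolment.
2. State that no waitlist school receives the intervention until a safety look has been reviewed.
3. Delete the words that place the interim ahead of the follow-up phase, and say that the look at complete T2 data governs waitlist delivery only.

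This costs a few sentences and faster data entry for the first batch. No alpha is spent as long as efficacy outcomes stay closed. The early look is imprecise: about ±0.23–0.24 SD on mean EDE-QS, against ±0.16–0.17 SD with all schools, if the pilot ICC and group size apply. A null result there is not evidence of safety and should not be reported as such. Item 2 may delay the first waitlist schools. With steady enrolment, half the schools would be enrolled by mid to late August 2026 (half of 705–735 days) and reach T2 three to five weeks later, in September or early October 2026. The first T3 could be due from June 2026. A smaller first batch would shorten that wait but reduce precision further.

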### Methods for additional analyses (e.g. subgroup analyses) {20b}

Subgroup analyses will be conducted based on baseline scores for each outcome variable, comparing participants with high versus low initial levels. In addition, moderator analyses will examine the potential influence of socioeconomic status (high vs. low), geographical area (urban vs. rural), and school type (state vs. private) on intervention effects.

### Methods in analysis to handle protocol non-adherence and any statistical methods to handle missing data {20c}

Little’s MCAR test [31] will be conducted to assess whether data are missing completely at random (MCAR). Participants who have more than 40% missing item responses on a given questionnaire will be excluded from analyses involving that specific measure but will remain included in other analyses where sufficient data are available.

If data are not missing at random, we will employ Multiple Imputation. The number of imputations will be decided based on m≈ %missing responses to items (as recommended by 32). Furthermore, we will run MNAR sensitivity analyses (pattern-mixture/delta) [33].

### Plans to give access to the full protocol, participant level–data, and statistical code {31c}

Anonymized data and analytic code will be shared on the Open Science Framework (OSF).

## Oversight and monitoring

### Composition of the coordinating centre and trial steering committee {5d}

This study is being conducted across multiple secondary schools in Colombia, through a collaborative partnership between Universidad del Norte (Barranquilla, Colombia) and Durham University (UK). The project is jointly designed and implemented by both institutions. Day-to-day support is provided by the principal investigator and the UK research team, who oversee the overall trial management.

Data management is a shared responsibility between the Colombian and UK teams, with data securely stored on both institutions’ servers. The study coordinator, [name] [name], leads the organization of data collection, school visits, data entry, and secure data storage.

The research team holds weekly meetings in various subgroups to coordinate ongoing activities and convenes monthly as a full team to review trial progress. Communication is maintained continuously through WhatsApp and email.

An international advisory group, composed of experts in the field, meets twice a year to provide strategic guidance and oversight. The advisory group is independent of the study. Several members of the advisory group have extensive statistical knowledge.

### Composition of the data monitoring committee, its role and reporting structure {21a}

No data monitoring committee (DMC) has been appointed for this study. Since this is not a blinded study in terms of whether a participant has been allocated to the intervention vs. control condition, or in terms of outcome assessments, no DMC is required to protect the blinding of researchers and participants.

### Adverse event reporting and harms {22}

Adverse events will be reported to the principal investigator (PI), who will promptly notify the local ethics committee and the advisory group. Any necessary protocol adjustments will be communicated to the entire research team.

In cases where an adverse event requires clinical intervention—such as if a child is triggered by discussions related to an unknown eating disorder—[name], a clinical psychologist on the local project team, will refer the child to appropriate clinical services.

### Frequency and plans for auditing trial conduct {23}

No auditing trial has been planned for this study, as it is not a common procedure in psychological body image interventions.

### Plans for communicating important protocol amendments to relevant parties (e.g. trial participants, ethical committees) {25}

All substantial amendments will be discussed within the research team and communicated to the relevant ethics committees and the advisory group. If amendments affect participants, they will be informed of the changes, and additional consent will be obtained when necessary. Trial registries will be updated accordingly to reflect these amendments. Funders will receive a final report; no interim updates or data will be shared with them prior to project completion.

### Dissemination plans {31a}

The results of this trial will be published in international peer-reviewed journals and presented at international conferences, regardless of the study outcomes. Participating schools will also receive summary reports detailing the findings.

## Discussion

Parental consent and written assent from adolescents will be obtained prior to collecting any data before and after the intervention activities. If parental consent cannot be secured, no outcome data will be collected from those adolescents. It will be the school’s decision whether these adolescents participate in the intervention activities or engage in alternative activities during that time.

In 2024, Colombia enacted a law (Ley 2383 de 2024) mandating the integration of socio-emotional education across the national school system, recognizing the importance of mental health initiatives in fostering children’s and adolescents’ socio-emotional development. The legislation requires structured activities to strengthen socio-emotional skills and promote mental and physical wellbeing [35]. This intervention aligns closely with the new legislation, making the present RCT a timely and valuable contribution to evaluating the effectiveness of a program designed to enhance media literacy and body esteem, thereby fostering resilience among young people.

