### Eligibility criteria {10}

Participants must meet the following criteria to be eligible for the study:Aged 11–17 yearsAttending a participating school and classWritten parental consentWritten child assent before the start of the studyIn school grade 7 to 10 (11–17-year-olds)Urban cluster: school is in an urban area, as classified by [13]Rural cluster: school is in a rural area [13]High socioeconomic status: schools located in areas defined as stratum (*estrato*) 4, 5, or 6Low socioeconomic status: schools located in areas defined as stratum (*estrato*) 1, 2, or 3.

If the participants meet any of the following criteria, they will not be eligible for the study:Aged ≤ 11 or ≥ 17 yearsDo not have written parental consentParticipants with mental health conditions (e.g. active eating disorders) are not excluded from the study; however, parents are explicitly advised to think carefully about whether consenting to their child’s participation in the study is in their best interests in this situation and not to give consent if they have any concerns.

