### Who will take informed consent? {26a}

Schools in Northern Colombia will be contacted by the research team and invited to participate in the study. Following approval from school principals, written study information will be distributed to parents. Parents will be required to provide written informed consent for their adolescent children to participate by returning a signed consent form to the team via the school or by completing a secure online form (hosted on Qualtrics). Adolescents (11–17-year-olds) will receive both written and verbal information about the study before filling out baseline questionnaires and will be asked to provide informed assent to participate. Only participants with valid parental consent and their own assent will be included in this study. Parental consent and adolescent assent will be collected by a member of the research team.

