## Assignment of interventions: blinding

### Who will be blinded {17a}

Participants, researchers, and facilitators will not be blinded, as it is impossible for them not to realize who received the intervention and who did not. Parental consent will be obtained prior to randomization. However, schools must be informed of the intervention schedule in advance to facilitate planning, allocate time for the sessions, and arrange travel. Participants will complete the questionnaires without prior knowledge of the upcoming intervention to minimize potential bias; they will be informed afterward regarding the timing and nature of the next activity.

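### A parent who withholds consent because of a child's eating disorder stops data collection, but as written the school may still place the child in the sessions

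*Protocol article*

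**What the plan says.** Eligibility criteria {10} states that participants "with mental health conditions (e.g. active eating disorders) are not excluded from the study". The safeguard offered in its place is advice to parents: they should think carefully about whether taking part "is in their best interests in this situation and not to give consent if they have any concerns".

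Who will take informed consent? {26a} sets the general requirement: "Parents will be required to provide written informed consent for their adolescent children to participate". The same section limits inclusion in the study to pupils who have both parental consent and their own assent.

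The Discussion says what follows when consent is missing. On data: "If parental consent cannot be secured, no outcome data will be collected from those adolescents". On attendance: "It will be the school’s decision whether these adolescents participate in the intervention activities or engage in alternative activities during that time".

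The sessions take place in class, during school hours. Under Explanation for the choice of comparators {6b}, waitlist schools receive the same programme after follow-up, so the attendance rule matters in both arms, though later in the control arm.

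**The concern.** The eligibility advice treats the parent's decision as the point at which a vulnerable child can be kept out. The Discussion does not carry that decision through to the classroom. Withholding consent takes the child out of the dataset, while a different party decides whether the child sits through the sessions.

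What is at stake is the safety of a small, identifiable group: pupils whose parents know of a condition and act on the protocol's own advice. Adverse event reporting and harms {22} itself gives, as an example of an event needing clinical help, a child triggered by session content because of an eating disorder nobody knew about. Where the condition is known and the parent has refused for that reason, the plan has a warning in hand and no rule that makes anyone act on it.

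**Working it through.** No arithmetic applies to the main point; it rests on reading the provisions together.

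**Step 1: what each parental decision leads to.**

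| Parent's position | In the study? | Outcome data? | Who decides on session attendance? |
|---|---|---|---|
| Consents (pupil assents) | Yes | Yes | Attends as a participant |
| Refuses on health grounds | No | No | School |
| Refuses data collection only | No | No | School |
| Does not return the form | No | No | School |

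The last three rows differ in what the parent wants, but the Discussion states a single rule for all of them. Only the second row is the case that the eligibility advice is meant to produce.

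**Step 2: does another provision give the parent a say over attendance?**

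- The Abstract and Who will take informed consent? {26a} keep pupils without consent out of the study. Neither keeps them out of the room.
- Principal approval and pupil assent come before any session, but neither is directed at a known condition.
- Criteria for discontinuing or modifying allocated interventions {11b} lets participants leave, and has facilitators watch for distress and remove affected pupils. This works only once the child is in the session.
- Adverse event reporting and harms {22} provides clinical referral, again after the event.
- Interim analyses {21b} allows stopping for a rise in eating disorder symptoms, but it draws on trial data and these pupils supply no outcome data.

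None of these restores the parent's decision before exposure.

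**Step 3: is there time to act on a parent's request?** Who will be blinded {17a} states: "Parental consent will be obtained prior to randomization". It adds that "schools must be informed of the intervention schedule in advance to facilitate planning, allocate time for the sessions, and arrange travel". A request to keep a child out can therefore be known before the sessions are scheduled.

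**Step 4: what a fix asks of a school.** Intervention description {11a} gives four sessions and says "Every session lasts 45 mins". For a class with at least one such pupil, supervision is at most 4 × 45 = 180 minutes, or 3 hours. A class with none needs no supervision. This is the cost of the remedy and does not measure the size of the problem.

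**The case against.** The strongest reply is that the provisions do not conflict. The eligibility advice is about consent to the study, the consent section is about inclusion in the study, and the Discussion agrees that a pupil without consent is not a participant. Leaving classroom attendance of non-participants to the school is an openly stated choice for a programme taught in school time. A reader might infer an outright contradiction; the text does not support that. What stands is narrower: the advice relies on refusal as protection, and the stated effect of refusal does not include protection.

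A reader might also infer that parents are misled, or that the forms have no way to decline. Neither can be known, because the information sheet, consent form and parent events are not shown and may already explain the school's role.

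The Discussion's wording about consent that could not be obtained may have been written with unreturned forms in mind. That is plausible, but the text makes no such restriction, and a refusal is also a case in which consent was not obtained.

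Finally, the risk should not be inflated. The protocol admits pupils with eating disorders whose parents agree, so it does not treat the condition as a contraindication. The pilot recorded no adverse events, and facilitators are trained to respond to distress. These points limit the residual risk and lower the severity, but they do not give the parent a say before exposure.

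**Conclusion.** The point holds in limited form. As written, a child whose parent refused on health grounds could still be placed in the sessions, because missing consent stops only outcome data and attendance is left to the school.

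It would go too far to say that such children will be exposed. The school may choose the alternative, and nothing obliges it to override a parent. Nor does the document show harm from attendance.

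The number of pupils concerned is unknown: the protocol gives no consent rate, no share of refusals on health grounds and no indication of how schools would decide, so no count is offered. The conclusion assumes that the Discussion's rule applies to active refusals as well as unreturned forms, and that no document outside the article already gives parents control over attendance. It is a minor participant-safety improvement with no effect on power, estimation or inference.

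**What to change.** Amend the Discussion so that, where a parent states that the child should not attend the sessions, the school must provide the alternative activities already mentioned there. No reason should be required. Keep school discretion for unreturned forms and for refusals limited to data collection, so that pupils whose parents object only to questionnaires need not miss the programme.

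State this in the advice to parents under Eligibility criteria {10}, and make sure that both the paper and the online consent form let a parent say so. If the forms already do, only the protocol text needs to change. Apply the same rule when waitlist schools receive the programme.

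The cost is a short ethics amendment, for which the protocol's section on communicating amendments {25} provides the route, and updated information for schools already recruited. Schools would supervise the pupils concerned for up to four 45-minute sessions per affected class. No outcome data are lost, since these pupils provide none under the present rule. Trial status puts the end of recruitment at August 2027, so the change can still reach schools yet to join and waitlist schools yet to receive the sessions.
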